Between April 2014 and July 2015, we conducted a pilot community-based, cluster randomized, open-label, controlled intervention trial in Rahim Yar Khan (RYK), Punjab, Pakistan to estimate the effect of an integrated newborn care kit (iNCK) versus the local standard of care (control) on all-cause neonatal mortality [14]. The intervention group received the iNCK via LHWs that visited pregnant women at home during the third trimester of pregnancy. The iNCK included a clean birth kit (CBK) which contained a plastic sheet, cord clamps, sterile blade, gloves, and soap. The iNCK also included 4% chlorhexidine (CHX) topical gel, sunflower oil emollient, a continuous temperature monitoring device called ThermoSpot™, a Mylar reflective blanket, and a reusable instant warmer. We also provided battery-operated scales to LHWs in intervention clusters to measure the newborns' weight. The study enrolled 2663 pregnant women in the intervention group and 2788 pregnant women in the control group [14]. There was no statistically significant difference in NMRs between the intervention and control clusters (risk ratio [RR] 0.83, 95% confidence interval [CI] 0.58–1.18; *p* = 0.30). However, several key findings emerged from the study: (1) using existing community health infrastructure to distribute the iNCK was a feasible delivery mechanism for the intervention; (2) the risk of fever and omphalitis in the intervention clusters was lower compared to the control clusters (RR 0.64, 95% CI 0.47–0.87, *p* = 0.004; and RR 0.68, 95% CI 0.48–0.98, *p* = 0.04, respectively); (3) by using the portable battery-operated weighing scales, LHWs in the intervention group reliably identified a higher proportion of low-birthweight babies among all babies who were delivered at home, which prompted appropriate follow-up care for the newborns (RR 3.48, 95% CI 1.00–12.10; *p* = 0.05); (4) ThermoSpot™ enabled caregivers to identify and act on cases of fever, cold stress, and hypothermia; and, (5) while the iNCK was almost always used, caregiver compliance to specific instructions on how to use the iNCK was low (for example, only 32% and 28% of participants in intervention clusters who used CHX and ThermoSpot™, respectively, started use on the first day of the newborn’s life, as instructed) [14]. Based on the results generated in the RYK pilot trial, further investigation into the implementation of the iNCK is warranted. Key questions that remain unanswered include whether the provision of a pictorial instruction guide will improve caregiver compliance, whether the iNCK can be used to deliver important maternal health interventions, and if the iNCK could have a beneficial impact in a remote, low population density, high mortality setting that has a seasonally cold climate.

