### The iNCK Intervention and Standard of Care Comparator

The iNCK includes a clean birth kit, 4% CHX topical gel, sunflower oil emollient, one ThermoSpot™ temperature monitoring sticker, a fleece blanket, a reusable instant heat pack warmer, three 200 μg dissolvable sublingual misoprostol tablets, a pictorial instruction guide, and a pictorial diary to mark daily use of iNCK components (Fig. 1). All of these components are packaged into a large resealable transparent plastic bag that is delivered by LHWs to enrolled participants in the intervention group. Additionally, each LHW assigned to the intervention group was provided with one handheld battery-operated scale to weigh newborns at their first post-delivery home visit. Table 1 provides a detailed description of the individual iNCK contents and their intended use.

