#### Sunflower oil emollient

The mother/caregiver will be directed to massage a small amount of sunflower oil (Synergy Crafts, Karachi) onto the baby's skin all over their body, avoiding the face and scalp, once per day, from the day of birth until day 28 of life. In low-income countries, sunflower oil has been proven to be effective in preventing hospital-acquired infections in preterm neonates and supporting their critically compromised skin barrier [23].

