#### Thermoindicator

The mother will be taught to place a ThermoSpot™ sticker (Maternova Inc, USA) over the carotid artery region of the newborn's neck on the day of birth and to use the sticker to continuously monitor the newborn’s body temperature until day 14 of life. She will be taught to reapply the sticker if it falls off before day 14. Additionally, she will be taught about the meaning of the different color responses, where a green face indicates normal temperature (36.5–37.5 °C), a pale green face indicates cold stress (36.0 °C–36.5 °C), a blue face indicates fever (> 39 °C), a red face indicates moderate hypothermia (35.0–35.5°C), and a black face indicates severe hypothermia (< 35°C). When the sticker turns pale green, the mother is educated to start kangaroo care, wherein she will place the baby skin-to-skin against her chest and monitor their temperature using the ThermoSpot™ sticker. Further, when the sticker turns red or black, the mother is instructed to place the newborn in the fleece blanket with the activated warmer and seek immediate medical care for the newborn. Caregivers will also be taught to seek immediate medical attention if the sticker turns blue, indicating that the baby has a fever. Several research studies have shown that ThermoSpot™ is effective in newborn temperature monitoring, especially in resource-limited areas [24, 25].

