### Study outcome measures

The primary outcome measure is all-cause neonatal mortality, defined as the death of a live-born child from any cause within the first 28 days of life. Study outcomes (Table 2) will be measured on all enrolled participants.

**Table 2 Tab2:** Primary and secondary outcomes

Primary Outcome	**•**All-cause neonatal mortality among live born neonates in first 28 days of life
Secondary Outcomes	**•**Cumulative incidence of omphalitis
	**•**Cumulative incidence of post-partum hemorrhage (PPH)
	**•**Post-delivery health facility utilization by pregnant women, and/or neonates and mothers in the first month postpartum
	**•**Cumulative incidence of hypothermia within the first 28 days of life, as identified through use of the ThermoSpot™, and explore the seasonal variability (by month) in the cumulative incidence of hypothermia **•**Cumulative incidence of fever within the first 28 days of life, as identified through use of the ThermoSpot™
	**•**Compliance with instructions on how to use the iNCK
	**•**Cause-specific neonatal mortality as determined by verbal autopsy

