### Statistical analysis plan

Hypothesis testing for this study will be based on a superiority framework and will be conducted at the α = 0.05 significance level. Primary analyses will be conducted using a complete-case, intention-to-treat approach, where participants will be analyzed in the trial arm their cluster was randomized to, irrespective of contamination or adherence to instructions on how to use the iNCK. The unit of analysis will be the individual neonate (neonatal mortality, omphalitis, fever, hypothermia, and healthcare utilization for newborn morbidities) or the individual woman (PPH and healthcare utilization for PPH). Risk ratios for the primary (neonatal mortality) and secondary (omphalitis and PPH) outcomes will be estimated using multivariable modified Poisson regression [29], with generalized estimating equations to account for the clustered design and robust variance estimators to account for multiple births and/or multiple pregnancies during the study period. Analyses of neonatal mortality (the primary outcome) will adjust for newborn sex, antenatal care, and gestational age at birth to improve power and efficiency; calendar time to account for underlying temporal trends (defined as month of birth, setting month of study launch as month 0); and the covariates used in the randomization procedure: GB study district, log cluster-specific baseline NMRs, and the cluster-specific baseline proportion of children delivered at a health facility. Analyses of omphalitis (secondary outcome) will adjust for newborn sex, antenatal care, and GB study district. Analyses of PPH (secondary outcome) will exclude women who delivered via C-section, and will adjust for parity, maternal age, history of prior C-section, history of prior PPH, GB study district, and the cluster-specific baseline proportion of women who reported experiencing PPH. The frequency of hypothermia, cold stress, and fever detected by ThermoSpot™ within the first 14 days of life will be described amongst participants in intervention clusters only, overall and by calendar month to assess seasonality. Finally, the frequency and location of health facility utilization for omphalitis, PPH, hypothermia, and fever will be described using counts and proportions amongst individuals experiencing each respective morbidity and will be stratified by trial arm. The proportion accessing healthcare services by trial arm will be compared using clustered t-tests and modified Poisson regression.

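### ThermoSpot frequencies of hypothermia, cold stress and fever are not tied to sticker wear, so they may understate incidence, and the monthly comparison may partly reflect wear

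*Protocol article*

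**What the plan says.** The Statistical analysis plan section states that the frequency of ThermoSpot-detected hypothermia, cold stress and fever "within the first 14 days of life will be described amongst participants in intervention clusters only, overall and by calendar month to assess seasonality". For the unit it says: "The unit of analysis will be the individual neonate (neonatal mortality, omphalitis, fever, hypothermia, and healthcare utilization for newborn morbidities".

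Table 2 (Study outcome measures) lists the matching secondary outcome as "Cumulative incidence of hypothermia within the first 28 days of life, as identified through use of the ThermoSpot™", with exploration of variation by month. The text above the table says that outcomes are measured on everyone enrolled.

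On wear, the Thermoindicator section has the mother apply the sticker on the day of birth and "continuously monitor the newborn’s body temperature until day 14 of life". The Rationale section reports from the pilot that "only 32% and 28% of participants in intervention clusters who used CHX and ThermoSpot™, respectively, started use on the first day". The plan also provides a day-by-day diary of component use (Table 1). Separately, the Statistical analysis plan section will describe uptake, timing and duration of use as compliance results. It does not link those results to the ThermoSpot frequencies.

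**The concern.** A newborn without a sticker on a given day can be hypothermic or febrile that day without being detected. If all intervention-arm neonates form the denominator, that newborn stays in the denominator but cannot enter the numerator for that day. The reported frequency then combines two things: how often temperature events occur, and how completely the sensor was worn.

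Two readings of the result are at stake. The first is the level: late starting was common among pilot users, so a figure called a cumulative incidence could be too low. The second is the seasonal pattern, the declared purpose of the monthly breakdown and relevant to a trial that gives a seasonally cold climate as part of its rationale. If wear changes from month to month, for example as teaching matures over about 26 months of enrolment, some of the apparent seasonal pattern could come from wear.

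**Working it through.** The article gives no figure for ThermoSpot incidence, wear time or monitored days, so there is nothing to reproduce. The calculation below only shows the possible range.

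**From the article:** 28% of pilot users started on day 1 (Rationale); the analysis window is 14 days (Statistical analysis plan).

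**Assumed:** true 14-day incidence of 20%; one detectable event day per affected newborn; that day is either uniform over days 1 to 14 or front-loaded, with weight on day d proportional to 0.7^(d−1); the other 72% start on day 2 or day 4; wear lasts to day 14 or for 7 days; every newborn is a user.

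**Formula:** let C(a) be the total event weight on worn days for a sticker started on day a.

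Coverage = 0.28 × C(1) + 0.72 × C(late start). Observed = 20% × coverage.

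**Worked example** (late start on day 4, worn to day 14):
- Uniform: C(1) = 1 and C(4) = 11/14 = 0.786. Coverage = 0.28 + 0.72 × 0.786 = 0.846, so observed = 16.9%.
- Front-loaded: the weights sum to 3.311, and days 1 to 3 hold (1 + 0.7 + 0.49)/3.311 = 0.661. C(4) = 0.339. Coverage = 0.28 + 0.72 × 0.339 = 0.524, so observed = 10.5%.

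| Late start | Wear | Uniform: coverage, observed | Front-loaded: coverage, observed |
|---|---|---|---|
| Day 2 | to day 14 | 0.949, 19.0% | 0.783, 15.7% |
| Day 4 | to day 14 | 0.846, 16.9% | 0.524, 10.5% |
| Day 2 | 7 days | 0.500, 10.0% | 0.724, 14.5% |
| Day 4 | 7 days | 0.500, 10.0% | 0.487, 9.7% |

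The relative shortfall runs from 1 − 0.949 = 5% to 1 − 0.487 = 51%. If 80% started on day 1, with the rest on day 4 and wear to day 14, coverage would be 0.957 (uniform) or 0.868 (front-loaded). Events that last or recur over several days would reduce the shortfall; never-users would increase it.

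**Months:** observed ratio = true ratio × (coverage in month A / coverage in month B). With no true difference, assumed coverages of 0.9 and 0.6 give 1.5, 0.7 and 0.6 give 1.17, and 0.8 and 0.8 give 1.0. If wear and event timing are the same in every month, incomplete wear leaves the ratio unchanged.

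**Why monitored time helps:** under uniform timing, day-1 events affect 20%/14 = 1.43% of newborns. With 28% wearing a sticker on day 1, detected day-1 events are 0.28 × 1.43% = 0.40% of all newborns. Dividing by the 28% observed returns 1.43%, provided that wearing is unrelated to risk.

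**The case against.** The best defence is that the sentence mainly says which arm is described, because only that arm has the sticker. The article does not define how non-wearers or unmonitored days are handled, and a descriptive secondary table may be specified in a fuller plan. The outcomes are also labelled as detected by ThermoSpot, and wear will be reported elsewhere. Part of this stands: a reader might infer a rule that scores unmonitored days as event-free, but the article states none. What remains is that the article does choose the population, the unit, the window and the monthly breakdown, calls the outcome a cumulative incidence measured on all enrolled, and leaves the wear data unconnected to it.

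Three stronger readings are tempting but unsupported.
- **Stickers are often lost.** The Thermoindicator section says "She will be taught to reapply the sticker if it falls off before day 14", and the kit holds "one ThermoSpot™ temperature monitoring sticker". Loss is foreseen, but no rate is given.
- **The daily oil massage conflicts with the sticker.** The oil is applied "all over their body, avoiding the face and scalp, once per day", which does not exclude the neck. However, the two instructions do not contradict each other, and nothing in the article says that oil detaches the sticker.
- **The seasonal pattern is confounded.** That needs wear to vary by month, for which there are no data. The ratios of 1.17 and 1.5 above follow from assumed coverages and are not expected effects.

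The 28% is also a pilot figure for start day among users. The Rationale says that the kit was almost always used, and this trial adds a pictorial guide intended to improve compliance. Whether the guide does so is listed there as an open question.

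**Conclusion.** The point holds in a limited form. As described, the ThermoSpot frequencies do not depend on wear, so they are frequencies of detected events and may understate incidence. Under the assumptions shown, the understatement lies between slight (about 5% relative) and about half. The documents do not allow a narrower statement. The monthly comparison may reflect wear if wear differs by month; late starting that is constant across months would not alter the ratios.

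The consequence is modest. The analysis is descriptive and single-arm, and neither the primary outcome nor any between-arm estimate of these events is affected.

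A neighbouring discrepancy is separate from this conclusion: Table 2 sets 28 days for hypothermia and fever, while wear and analysis cover 14. Under the 28-day definition even perfect wear would observe 14/28 = 50% of the period, so those passages need to be reconciled.

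**What to change.** In the Statistical analysis plan section, keep the all-participant frequency and add:

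1. the frequency of hypothermia, cold stress and fever among newborns with a sticker applied;
2. the same events per monitored day, preferably by day of life, because a crude rate gives late starters mainly the later days;
3. a calendar-month comparison based on monitored time, with sticker uptake, start day and duration of wear shown by month beside it.

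The daily diary ticks and the planned description of timing and duration of use should supply the monitored time without new data collection. The article does not say whether each temperature event is dated; if it is not, the breakdown by day of life may not be possible.

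The cost is a few extra table rows and some derivation work. There are two drawbacks: the estimates depend on the completeness of self-reported diaries, and restricting to wearers may introduce some selection. Keeping the all-participant figure alongside lets readers judge both.

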### Delivery of the integrated neonatal care kit

As part of their routine activities, LHWs identify pregnant women and record the first day of their last menstrual period. As part of their mandate, LHWs already register all pregnant women in their catchment area within the first trimester of pregnancy. On a monthly basis, LHWs report the number of newly identified pregnancies to their Lady Health Supervisor (LHS).

To efficiently capture pregnancy data and enable timely iNCK delivery and subsequent data collection, our research team will provide LHSs across each of the seven districts with a pregnancy identification form to document the pregnant woman’s name, address, and phone number. LHSs will distribute these forms to LHWs, who will in turn complete them during home visits when they first identify new pregnancies. The information enables study-employed data collectors to locate the appropriate households to screen for eligibility, obtain written consent, and enroll participants, and for field supervisors to contact the mothers/caregivers directly to schedule data collection visits.

During this same visit, and after collecting written informed consent, LHWs will provide the iNCKs to participants in intervention clusters, educate them on how to use the kit components plus provide the local standard of care. The LHW will be directly observed during these activities by a trained data collector who will complete an evaluation of the process. Participants who reside in control clusters will not receive iNCKs but will receive the local standard of care from LHWs. To facilitate the timely and reliable notifications of new births, at the time of consent, all participants will be provided with contact information and instructions to notify the study team and/or their LHWs as soon as possible following delivery.

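### Facility use appears to be tested between arms only among people with the morbidity: fever and hypothermia have no control-arm case definition, and omphalitis and PPH are outcomes the kit is meant to reduce

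*Protocol article*

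**What the plan says.** Table 2 (Study outcome measures) lists as a secondary outcome "Post-delivery health facility utilization by pregnant women, and/or neonates and mothers in the first month postpartum". It does not limit this to people with a morbidity, and the sentence introducing the table says that outcomes are measured on everyone enrolled.

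The Statistical analysis plan section is narrower. For omphalitis, PPH, hypothermia and fever, the frequency and location of facility use "will be described using counts and proportions amongst individuals experiencing each respective morbidity and will be stratified by trial arm". It continues: "The proportion accessing healthcare services by trial arm will be compared using clustered t-tests and modified Poisson regression". No denominator is given for that test.

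Three other statements bear on who can be a case:

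- Table 2 gives the fever outcome as "Cumulative incidence of fever within the first 28 days of life, as identified through use of the ThermoSpot™", and words hypothermia in the same way.
- Delivery of the integrated neonatal care kit: "Participants who reside in control clusters will not receive iNCKs but will receive the local standard of care from LHWs". ThermoSpot is part of the kit.
- Statistical analysis plan: the frequency of ThermoSpot-detected hypothermia, cold stress and fever "within the first 14 days of life will be described amongst participants in intervention clusters only".

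For the pilot trial, the Rationale reports that "the risk of fever and omphalitis in the intervention clusters was lower compared to the control clusters", with RR 0.64 for fever and 0.68 (95% CI 0.48 to 0.98) for omphalitis.

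**The concern.** There are two separate problems.

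For hypothermia and fever, the section restricts ThermoSpot events to intervention clusters and then stratifies care-seeking for the same conditions by arm. On the article's definition the control arm has no cases. If control cases are found in some other way, that way is not stated and differs from the one used in the intervention arm.

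For omphalitis and PPH, cases can exist in both arms, but the kit is meant to prevent them. Clusters were randomised, not the subset of babies with omphalitis or women with PPH. If the kit changes which cases occur, the remaining case groups differ in severity, and severity drives care-seeking. A difference in the proportion seeking care could then appear with no change in behaviour, or a real change could be hidden. At stake is the interpretation of one tested secondary outcome: whether the kit changes facility use.

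**Working it through.** The article states no figure for care-seeking, so there is none to reproduce. The check is a reading of the text followed by an illustration.

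**Hypothermia and fever.** No arithmetic is needed. A case is a ThermoSpot reading (Table 2). Control families have no ThermoSpot (Delivery section). ThermoSpot frequencies are limited to the intervention arm, yet care-seeking for these conditions is presented by arm (both in the Statistical analysis plan section). These statements cannot all stand without a separate control-arm definition.

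**Omphalitis.** The only documented input is the pilot incidence RR of 0.68. The rest are assumptions: a share *s* of control cases is severe (20%, 30% or 50%); mild and severe cases seek care with probabilities *m* and *v* (30% and 80%, or 40% and 90%), identical in both arms; the kit prevents mild cases only. Per control case:

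- control proportion seeking care: (1 − s)m + sv
- intervention proportion seeking care: [(0.68 − s)m + sv] / 0.68
- all-births RR = 0.68 × among-case RR

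Worked for s = 0.3, m = 0.3, v = 0.8:

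- control: 0.7 × 0.3 + 0.3 × 0.8 = 0.450
- intervention: (0.38 × 0.3 + 0.24) / 0.68 = 0.354 / 0.68 = 0.521
- among-case RR: 0.521 / 0.450 = 1.16
- all-births RR: 0.354 / 0.450 = 0.79

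| s | m, v | Control | Intervention | Among-case RR | All-births RR |
|---|---|---|---|---|---|
| 0.2 | 0.3, 0.8 | 0.400 | 0.447 | 1.12 | 0.76 |
| 0.2 | 0.4, 0.9 | 0.500 | 0.547 | 1.09 | 0.74 |
| 0.3 | 0.3, 0.8 | 0.450 | 0.521 | 1.16 | 0.79 |
| 0.3 | 0.4, 0.9 | 0.550 | 0.621 | 1.13 | 0.77 |
| 0.5 | 0.3, 0.8 | 0.550 | 0.668 | 1.21 | 0.83 |
| 0.5 | 0.4, 0.9 | 0.650 | 0.768 | 1.18 | 0.80 |

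Behaviour at each severity is the same in both arms throughout, yet the among-case RR is 1.09 to 1.21 while the all-births RR is 0.74 to 0.83. The two denominators point in opposite directions.

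**More detection in one arm.** Suppose control cases of fever or hypothermia were found without a sticker, and the sticker reveals *f* times as many mild cases (s = 0.3, m = 0.3, v = 0.8; all assumed). The intervention proportion is (0.7f × 0.3 + 0.24) / (0.7f + 0.3), against 0.450 in control:

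- f = 1.5: 0.411, RR 0.91
- f = 2: 0.388, RR 0.86
- f = 3: 0.363, RR 0.81

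Detection alone therefore pushes the among-case RR below 1.

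**PPH.** The same reasoning applies, but the article gives no effect of the kit on PPH, and the pilot kit as listed held no misoprostol. No size is computed.

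**The case against.** The strongest reply is that the tested denominator is inferred. The sentence naming the case-only denominator is descriptive; the sentence with the test names none. The same section makes the individual neonate or woman the unit of analysis, and a fuller plan may exist. This stands as a limit on certainty: a reader might infer that the article expressly confines the test to cases, and it does not. But the test follows directly on the case-only sentence, and no wider comparison is given.

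Second, whether affected babies and women reach care is a sensible question and is inherently conditional, whereas an all-births proportion falls when the kit prevents disease. This also stands. It is a reason to show both measures, not to test the unprotected one alone.

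Third, live birth also comes after randomisation. True, but the kit's stated targets are infection, temperature and maternal bleeding. What matters is whether the kit changes the denominator, and live birth is far less exposed to that than omphalitis or PPH.

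Fourth, the pilot compared fever between arms, so a control-arm measure is feasible. Agreed, but this article's definition is the sticker.

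A reader might also extend the point to "Analyses of PPH (secondary outcome) will exclude women who delivered via C-section" as a breach of intention-to-treat. The documents do not support that. Misoprostol is to be taken after the baby is delivered, no kit route to mode of delivery is shown, and the section defines intention-to-treat by the arm of the randomised cluster irrespective of contamination or adherence, which this exclusion leaves intact.

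**Conclusion.** The point holds. For hypothermia and fever, the by-arm comparison is wrong as written: it has no control cases on the article's own definition, or it relies on different ascertainment in each arm. For omphalitis and PPH, a test among cases, which is the natural reading, is not protected by randomisation.

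The size is illustrative. Under the assumed severity mixes, with identical behaviour in both arms, the among-case RR for omphalitis is about 1.1 to 1.2; under the assumed extra detection of mild fever or hypothermia it is about 0.8 to 0.9. Only the 0.68 comes from the document. If prevention were unrelated to severity, the omphalitis RR would be 1.00, so bias is possible rather than certain, and its direction cannot be fixed in advance. A reader might infer much larger distortions by supposing that no prevented or newly detected case would have sought care. Nothing in the documents supports that, and caregivers are taught to seek care on certain sticker colours.

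This concerns a secondary outcome. The primary mortality analysis is unaffected.

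**What to change.** Reword the care-seeking part of the Statistical analysis plan section:

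1. Make the between-arm test one of facility use for each condition in the first month over all live-born neonates or, for PPH, over all women in the PPH analysis set. This matches the population in Table 2.
2. Report among-case proportions by arm as description, without a test, beside the result in 1.
3. Describe care-seeking for ThermoSpot-detected hypothermia and fever in the intervention arm only. Alternatively, compare arms only on a caregiver-reported definition collected identically in both, and state it. Even then the sticker may change what caregivers notice, so the limitation should be acknowledged.

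The cost is mainly wording. The day-29 visit collects secondary outcomes in both arms. In item 1 the numerator is unchanged, since anyone without the condition counts as having no visit for it. The forms are not shown, so whether both arms receive the same fever and hypothermia questions must be confirmed before the second option in item 3 is chosen. The downside is that the all-births measure mixes incidence with care-seeking, which is why both measures should appear together.
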